## Abstract

**Background:**

Chronic obstructive pulmonary disease (COPD) accounts for 10–12 % of primary care consultations, 7 % of hospital admissions and 35 % of chronic incapacity related to productivity. The misuse of inhalers is a significant problem in COPD because it is associated with reduced therapeutic drug effects leading to lack of control of both symptoms and disease. Despite all advice, health care professionals’ practice management of inhalation treatments is usually deficient. Interventions to improve inhaler technique by health care professionals are limited, especially among primary care professionals, who provide the most care to patients with COPD. The aim of this study is to evaluate the efficacy of an educational intervention to train general practitioners (GPs) in the right inhalation technique for the most commonly used inhalers.

**Methods/design:**

We are conducting a pragmatic cluster randomised controlled trial. The sample population is composed of 267 patients diagnosed with COPD using inhalation therapy selected from among those in 20 general practices, divided into two groups (control and intervention) by block randomisation at 8 primary care centres. The sample has two levels. The first level is patients with COPD who agree to participate in the trial and receive the educational intervention from their GPs. The second level is GPs who are primary health care professionals and receive the educational intervention. The intervention is one session of the educational intervention with a monitor given to GPs for training in the right inhalation technique. The primary outcome is correct inhalation technique in patients. Secondary outcomes are functional status (spirometry) and quality of life. The follow-up period will be 1 year. GPs will have two visits (baseline and at the 1-year follow-up visit. Patients will have four visits (at baseline and 3, 6 and 12 months). Analysis will be done on an intention-to-treat basis.

**Discussion:**

We carried out three previous clinical trials in patients with COPD, which showed the efficacy of an educational intervention based on monitor training to improve the inhalation technique in patients. This intervention is suitable and feasible in the context of clinical practice. Now we are seeking to know if we can improve it when the monitor is the GP (the real care provider in daily practise).

**Trial registration:**

ISRCTN Registry identifier ISRCTN93725230. Registered on 18 August 2014.

## Background

Chronic obstructive pulmonary disease (COPD) accounts for 10–12 % of primary care consultations, 35–40 % of hospital consultations, 7 % of hospital admissions and 35 % of disability related to productivity [1]. The disease cost represents 2 % of the annual budget of the Ministry of Health and Consumer Affairs in Spain [1], and in the European Union the total costs of respiratory disease are estimated to be about 6 % of the total health budget; 56 % of this cost is due to COPD [2]. Two thousand euros per year has been estimated as the mean direct cost generated by these patients. The major part (43.8 %) corresponds to hospital admissions, followed by controlled drug consumption (40.8 %) in patients with mild COPD. This percentage decreases to 37.4 % and 28.4 % in patients with Global Initiative for Chronic Obstructive Lung Disease (GOLD) stages III and IV, respectively [3].

The administration of drugs using inhalation technologies has changed the treatment of respiratory diseases. These drugs have advantages over systemic therapy, including faster delivery to the targeted organ and reduction of side effects [4]. The effectiveness of inhaled drugs can be influenced by numerous factors, which are mainly age, sex, education level, years of diagnosis, type of inhaler, use of the right inhalation technique or use of different devices [5, 6].

The misuse of inhalers is a significant problem in asthma and COPD because it is associated with reduced therapeutic drug effects leading to a lack of control both symptoms and disease [7–10]. If patients are prescribed a treatment without proper training, a less than optimal therapeutic effect results [10, 11].

Even though clinical practice guidelines advocate the implementation of health education programmes during medical follow-up, in some studies researchers have observed that more than 85 % of patients do not correctly use their inhalers [11–14]. The educational interventions proposed by these guidelines must include aspects such as positive reinforcement, smoking cessation advice, diet and exercise information, adherence to the therapeutic regimen and verification of the right inhalation technique [15, 16].

International guidelines on the management of COPD refer to the following aspects related to the inhalation technique [2, 17, 18]. (1) The effectiveness of the bronchodilator therapy should be assessed on the basis of not only the pulmonary capacity of the patient but also other aspects, such as improvement of symptoms, improvement in daily activities, capacity to perform exercise and self-control of the symptoms. (2) Most of the patients, independently of age, can learn to use the proper inhalation technique with appropriate training. (3) Once the patient has shown the ability to perform the right inhalation technique, the device should be prescribed. (4) The patient’s ability to use devices must be checked regularly by highly trained health care professionals, and, if necessary, the patient must be retrained in the proper inhalation technique.

Despite these recommendations, the use of inhaler devices by health care professionals is deficient [10, 19]. Interventions to improve inhalation technique in health care professionals are limited, especially among primary health care professionals, who provide care to most patients with COPD [19, 20].

### Study aims

Our research group has studied the management of chronic illness in primary care for more than 15 years, focusing mainly on COPD. The first step taken was to carry out trials to develop tools to assess therapeutic adherence and educational interventions to improve adherence. Our first educational intervention was designed with three components (motivational and cognitive aspects, as well as skill development in inhalation techniques). The intervention was evaluated in a randomised controlled trial which showed that treatment adherence improved by 48 % (relative risk) with a number needed to treat (NNT) of 6.37 [14]. In the last 3 years, our clinical trials have been focused on the evaluation of educational interventions to improve inhalation techniques in patients with COPD. We have designed two educational interventions to improve inhalation technique: (1) only written information (leaflet) or (2) written information (leaflet) reinforced by instructor training. These trials showed that an intervention with a demonstration by a trainer is significantly more effective than an informative leaflet alone, with an increase in the number of patients who develop proper inhalation technique by 48 % at 3 months and by 41 % at 1-year follow-up [21].

The next step is the start-up of an intervention focused on primary health care professionals so that they are well-trained. The main goal is to evaluate the efficacy of an educational intervention to train general practitioners (GPs) in the right inhalation technique for the most commonly used inhalers and, afterwards, to evaluate the improvements in inhalation techniques performed by their patients. The secondary outcomes of this intervention will be a clinical control improvement and follow-up of the disease as well as improvement in health-related quality of life. All of these outcomes have been key goals for more than 10 years.

### Study hypothesis

On the basis of current published evidence, inhalation techniques in patients with COPD are insufficient, and this overlaps with a lack of well-trained health care professionals. Our working hypothesis is that providing an educational intervention to primary care professionals (GPs) will increase by at least by 25 % the number of patients who report use of the correct inhalation techniques compared with a control group of patients receiving standard care.

## Methods/design

### Overview

This study is a pragmatic cluster randomised controlled trial (Fig. 1). There are various circumstances in which the pragmatic cluster randomised controlled trial has shown to be the most appropriate design, particularly when health programmes are more focused on the organisational level. This design can also avoid “contamination” between patients when an educational intervention is applied in a primary care centre, owing to its having been individually randomised. This contamination is due to communication between participants, which can change the real effect of the intervention. Finally, when educational strategies for the right patient control are focused on health care professionals, the only adequate strategy is the randomised allocation of them [22, 23].

**Fig. 1 Fig1:**
[figure not shown]
Study scheme. *COPD* chronic obstructive pulmonary disease

For our trial, the cluster design is based on two levels: the higher or second level, represented by the GP (who will receive the educational intervention), and the lower or first level, represented by the GP’s patients (who have agreed to participate and will receive the educational intervention from their GP).

### Participants

A total of 267 patients diagnosed with COPD and receiving inhalation therapy will be selected from 20 general practices in 8 primary care centres in Málaga and Almería, Spain. This sample size is enough to detect a 25 % difference between groups regarding the right performance of inhalation technique, with a power of 80 % and a confidence level of 95 %. The sample size was adjusted according to the standard criteria for cluster randomised trials, using the design effect (DE) of 2.3. The DE was calculate as follows: DE = 1 + (*n*_c_ – 1) × ICC (where *n*_c_ is the mean number of individuals in the cluster and ICC is the intra-cluster correlation coefficient). The ICC in the present work was considered to be 0.1, and the mean cluster size was assumed to be 10 [24–26]. A potential loss of 40 % was estimated. Therefore, inclusion of 267 patients and 20 GPs will be required, with all of them signing consent forms to participate in the study.

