### Study limitations

The first limitation is about the actual study design. In pragmatic cluster randomised controlled trials, the first bias to take into account is the selection bias, as the randomisation is usually applied in the second level, before recruitment of the first-level participants, which is where the intervention impact is measured. However, there are strategies that minimise this bias, and we are using these in this study. First, the selection and follow-up of patients (patient inclusion visit and visit 1) will be carried out by an external researcher who will have no knowledge of GP randomisation. Second, the effect of the intervention over recruitment can lead to different recruitment indexes, depending on the groups, due to the possibility that GPs in the control group could be less motivated to participate. Moreover, to avoid different recruitment indexes in both groups, once the trial is finished, the GPs in the control group will be trained in the same way as the study group professionals were trained (if the intervention shows a significant improvement in patients) [23, 32].

Another study limitation is the potential for loss to follow-up. To minimise these losses, patients will be contacted at least three different times and at different times of day. However, loss to follow-up was taken into account in the sample size calculation and will be taken into account in performing data analysis (intention-to-treat analysis).

Another bias is the Hawthorne effect, which relates to how participants in a study change their behaviour under observation. However, we believe that the effect of this bias will be minimal because of patients’ being trained and followed by their GPs, with the exception of the inclusion and final visits. Besides, there is a control group in which the follow-up will permit us to minimise the real impact of this bias.

There could be measurement bias due to mistakes in recording of some variables or interviewer bias due to the administration of the questionnaires. To minimise these biases, interviewers will have been trained previously to ensure that visits will be as homogeneous as possible. A DCF and a manual that explains how each variable is measured at the follow-up visits will be given to the GPs in the intervention group.

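### The sample size is internally inconsistent (the printed inputs give a design effect of 1.9, not 2.3), and neither 267 nor the 80% power can be reproduced because no control rate is stated

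*Protocol article*

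**What the plan says.** All the sizing figures are in the Participants section of the protocol article.

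- Target: "This sample size is enough to detect a 25 % difference between groups" in correct technique, "with a power of 80 % and a confidence level of 95" per cent.
- Clustering: the total was adjusted "using the design effect (DE) of 2.3". The formula printed is DE = 1 + (n_c − 1) × ICC, and "The ICC in the present work was considered to be 0.1, and the mean cluster size was assumed to be 10".
- Loss: 40% is anticipated. The Study limitations section repeats that "loss to follow-up was taken into account in the sample size calculation".
- Result: "inclusion of 267 patients and 20 GPs will be required".

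No control-group rate, no unadjusted sample size and no account of how the 40% was applied are given. The only rate nearby is in the Background, where some studies found more than 85% of patients using inhalers incorrectly, that is, fewer than 15% correct.

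The Study hypothesis words the effect differently. The intervention is to "increase by at least by 25 % the number of patients" who report correct use, whereas the primary outcome under Study variables is an observed step-by-step test.

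**The concern.** The four clustering figures are printed together and disagree, so condensing a longer protocol into an article does not explain the conflict. The total and the power claim rest on them.

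The larger issue is the 40% loss. If it was not built into 267, the trial would have 80% power only if nobody were lost, while the plan expects about 160 patients at the end. A null result could then be read as well-powered evidence of no 25-point effect when the real power was lower. As printed, a reader cannot tell whether this is so.

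**Working it through.** **1. Design effect from the stated inputs.** 1 + (10 − 1) × 0.1 = 1.9; the plan states 2.3. Solving for 2.3:
- at ICC 0.1, n_c = 1 + 1.3/0.1 = 14;
- at n_c = 10, ICC = 1.3/9 = 0.144.

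**2. Cluster size from the totals.**
- Enrolled: 267/20 = 13.35 per GP, DE = 1 + 12.35 × 0.1 = 2.235.
- After 40% loss: 267 × 0.6 = 160.2, or 8.01 per GP, DE = 1 + 7.01 × 0.1 = 1.70.
- The stated 10 per GP would give 20 × 10 = 200 patients.

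The assumed 10 matches neither the enrolled nor the retained figure.

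**3. Attempt to reproduce 267.** Inputs: a 25-point absolute difference, two-sided α 0.05 (sidedness is not stated; assumed), power 80%, 1:1 allocation. With p̄ = (p₁ + p₂)/2, the pooled-variance formula is

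n per arm = [1.96√(2p̄(1−p̄)) + 0.842√(p₁(1−p₁) + p₂(1−p₂))]² / (p₂−p₁)²

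For 25% versus 50%: (1.96 × 0.6847 + 0.842 × 0.6614)² / 0.0625 = 57.7, so 58 per arm. 50% versus 75% gives the same. Then 2 × 58 × 2.3 = 266.8, which rounds up to 267 with no allowance for loss. Adding the loss gives 266.8/0.6 = 445.

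Other assumed control rates reach about the same total with the loss included as division by 0.6:

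| Control vs intervention | n per arm | DE | Total with 40% loss |
|---|---|---|---|
| 4% vs 29% | 34 | 2.3 | 260.7 |
| 5% vs 30% | 36 | 2.3 | 276.0 |
| 9% vs 34% | 42 | 1.9 | 266.0 |
| 10% vs 35% | 43 | 1.9 | 272.3 |
| 13% vs 38% | 47 | 1.7 | 266.3 |

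So at the stated DE of 2.3 the loss fits only at a control rate of about 5% or lower. (The formula is symmetric, so about 70% or higher would also do, but the Background figure points away from that.)

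**4. Power with 160.2 analysed.** The effective n per arm is m = 80.1/DE, and

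power = Φ{[0.25√m − 1.96√(2p̄(1−p̄))] / √(p₁(1−p₁) + p₂(1−p₂))}

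Example, 25% versus 50% at DE 2.3: m = 34.83, (0.25 × 5.901 − 1.342)/0.6614 = 0.20, power 0.58.

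| Assumed control rate | DE 2.3 | DE 1.9 | DE 1.7 |
|---|---|---|---|
| 5% | 0.797 | 0.869 | 0.904 |
| 10% | 0.714 | 0.796 | 0.839 |
| 13% | 0.675 | 0.759 | 0.805 |
| 15% | 0.653 | 0.738 | 0.785 |
| 25% | 0.580 | 0.665 | 0.714 |
| 37.5% | 0.552 | 0.636 | 0.685 |

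For comparison, with all 267 analysed at DE 2.3, power is 0.803 at a control rate of 25%.

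**5. Detectable difference.** Setting the same formula to 80% power with 160.2 analysed and DE 1.70 gives about 23.5 points at a control rate of 10%, 25.5 at 15% and 27.8 at 25%.

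**The case against.** A reader might infer that the 40% loss was plainly forgotten, since 2 × 58 × 2.3 lands on 267. The documents do not support that as a fact. Neither 116 nor a 25% or 50% control rate appears anywhere, and two sections say that loss was allowed for. The only rate in the text, below 15% correct in some studies, fits 25% or 50% poorly. Lower control rates reach about 267 with the loss included. Other conventions widen the possibilities: inflating by 1.4 instead of dividing by 0.6 gives 2 × 42 × 2.3 × 1.4 = 270.5 at 9% versus 34%. This objection stands. What remains is that no listed route with the loss included uses the printed 2.3 as exactly as the route without it.

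A reader might also infer that the trial is shown to be underpowered. It is not: at DE 1.7, the value matching 8 completers per GP, 80% is met up to a control rate of about 13%.

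Nor does the design-effect slip itself cost power, since 2.3 asks for more patients than 1.9. The slip may lie in the cluster size: 14 per GP gives 2.3 exactly, and 267/14 = 19.07 rounds up to 20 GPs. That is plausible, but the text does not settle it.

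Finally, the Study hypothesis could be read as a relative 25% increase in self-reported use. The Participants section sizes a between-group difference in performance and the outcome is an observed test, so this is loose wording and not a second sizing target.

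**Conclusion.** Two contradictions are certain from the text alone: the stated inputs give a design effect of 1.9 against 2.3 printed, and the totals give 13.35 patients per GP against 10 assumed. Which figure is wrong cannot be determined.

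The 267 and the 80% power are untraceable, which is different from being shown to be wrong. Omission of the 40% loss is a reasonable suspicion only. With the loss the plan expects, power for 25 points runs from about 55% to 90% over assumed control rates of 5% to 37.5% and design effects of 1.7 to 2.3. From 15% to 37.5% it is below 80% at every design effect tried. These figures assume a two-sided 5% test, an absolute 25-point difference, equal arms and about 160 patients analysed; the control rates are assumptions.

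The correction is needed because the power claim for the primary outcome depends on these inputs.

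**What to change.** Keep 267 patients and 20 GPs. In the Participants section:

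- give one consistent set of cluster size, ICC and design effect (at ICC 0.1, 13.35 enrolled per GP gives 2.235 and 8.01 retained gives 1.70);
- state the assumed control rate, the unadjusted number per arm and the sidedness of the test;
- say how the 40% loss was applied;
- restate the power for 25 points, or the detectable difference, that follows from those inputs.

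In the Study hypothesis, word the 25% as the same absolute difference in observed technique, replacing "the number of patients who report use of the correct inhalation techniques compared with a control group" with wording that matches the step-by-step test.

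The cost is a text correction with no extra patients or GPs. The restated power may be less favourable than 80%, depending on the control rate that was actually assumed.

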#### First-level participants: patients

##### Inclusion and exclusion criteria

The inclusion criteria are a COPD diagnosis, being treated at the primary care centres included in the trial, being prescribed inhalation therapy and consenting to participate in the trial by signing the informed consent form. The exclusion criteria are having another respiratory illness not included in the COPD definition and having cognitive impairments which prevent the individual from completing the outcome questionnaires or engaging with the educational intervention.

##### Recruitment

For recruitment, potentially eligible patients will be identified through a search of practise electronic records by research assistants. Eligible patients will receive a brief explanation of the intent of the study by phone, and, if they are interested, they will be given an appointment at their primary care centre for a more detailed explanation. Once the consent form has been signed, the patient’s inclusion visit will be carried out and all the variables will be measured (including the evaluation of the inhalation technique of all inhalers the patient uses). For eligible patients who decline to participate, basic information (age, sex, reason for declining) will be collected from the practice to allow examination of response bias.

##### Follow-up

The follow-up of patients will be limited to 1 year after the inclusion visit by the research team. During the inclusion visit, all variables will be measured again, including the evaluation of inhalation techniques. All measurements will be taken by a research assistant who has no knowledge of either the randomisation of the GPs or whether the patients belong to the study or control arm.

##### Interventions in patients

The patients included in the intervention group will receive an educational intervention from their GPs, who will train them in the correct use of their devices. This intervention will consist of the following:Performance of inhalation techniques to detect mistakes that will be registered on a specially designed sheetDemonstration of proper inhalation techniquesIdentification of mistakes in technique and opportunities to ask health professionals about how to perform inhalation properly

The patients will be given an appointment for reinforcement visits at 3 and 6 months after the inclusion visit. In these visits, the GPs will encourage and refresh their performance of inhalation techniques.

As the educational intervention will not be blinded, the external researcher responsible for collection of patient data will not know the patient allocation. The patients included in the control group will follow the standard clinical practice.

#### Second-level participants: GPs

##### Inclusion and exclusion criteria

The inclusion criteria for second-level participants are that they must be doctors who care for patients included in the COPD Process of Andalusian Health Service Guidelines (COPD PAI) [16], use prescribed inhalation therapy and have consented to participate. The exclusion criteria are refusal to participate in the trial or having to leave the job during the trial.

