##### Recruitment and randomisation

For the selection of GPs, the research project will rely on pre-selected primary care centres. Twenty GPs will be selected by using a non-probabilistic consecutive sampling method: 10 GPs as the control group and 10 GPs as the study group. To do that, GPs will be invited to participate and will be included in either group by using a block randomisation technique. Each block is formed by four GPs among whom the two study arms will be uniformly distributed. Once the blocks have been created, they will be distributed using a sequence of random numbers and the final list of GP allocations will be created. The final list of GP allocations will be guarded by the principal investigator of the project, and he will inform the allocation of each GP included in the trial.

The GP’s inclusion visit will be carried out once the randomisation has been done. In this visit, all of the study’s variables are collected and the inhalation technique of each inhaler is evaluated through a specific step-by-step test. This test was specially designed for this study on basis of the Sociedad Española de Neumología y Cirugía Torácica (SEPAR) recommendations [4] for most of the commonly used devices (Spiriva HandiHaler, Boehringer Ingelheim, Ridgefield, CT, USA; Seretide Accuhaler, GlaxoSmithKline, Philadelphia, PA, USA; turbuhalers; pressurized metered-dose inhalers; and Breezhaler, Novartis, Basel, Switzerland).

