### Statistical analysis

#### General

A descriptive statistical analysis will be performed for all study variables. We will calculate the means, medians and standard deviations for quantitative variables and the absolute and relative frequencies for qualitative variables. The 95 % confidence interval will be applied. The analysis will be done according to the intention-to-treat principle. The baseline comparison will be made between the main variables that we expect to be related to the primary outcome using the χ^2^ test or analysis of variance (ANOVA).

At the first level, the between-group comparison for the primary outcome will be explored using the χ^2^ test. Relative risk reduction, absolute risk reduction and NNT will be calculated. Inferences for secondary outcomes will be made using ANOVA or the χ^2^ test.

Finally, a logistic regression model will be used for the primary outcome (performance of the right inhalation technique [yes or no]), considering the intervention as the predictive variable and the rest of the independent measures as the possible modifying factors. We will use the usual 5 % significance level (α = 0.05) and the SPSS version 15.0 statistical software package (SPSS, Chicago, IL, USA) to run the proposed analysis.

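### A GP exclusion for leaving the post while the trial runs, read literally, acts after randomisation and conflicts with the intention-to-treat analysis

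*Protocol article*

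**What the plan says.** The eligibility rule for the second-level participants (Second-level participants: GPs, Inclusion and exclusion criteria) reads: "The exclusion criteria are refusal to participate in the trial or having to leave the job during the trial".

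The next section, Recruitment and randomisation, makes the GP the unit of allocation: "GPs will be invited to participate and will be included in either group by using a block randomisation technique". The split is "10 GPs as the control group and 10 GPs as the study group". It also fixes the order of events: "The GP’s inclusion visit will be carried out once the randomisation has been done". The GP Follow-up section sets a second visit one year after the inclusion visit.

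On the analysis, Statistical analysis, General states: "The analysis will be done according to the intention-to-treat principle". Study limitations returns to this and says that "loss to follow-up was taken into account in the sample size calculation and will be taken into account in performing data analysis (intention-to-treat analysis".

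The patients have their own eligibility criteria, and a change of GP is not among the exclusions. The patient Follow-up section has the research team follow patients for a year, with all measurements made by a research assistant who does not know the allocation. Study limitations says that an external researcher, unaware of the GP randomisation, carries out the inclusion visit and visit 1.

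**The concern.** An eligibility criterion should be decidable before allocation. Whether a GP leaves during the following year is in general known only afterwards. Because the GP is the randomised cluster, applying the rule to an actual departure would take a randomised unit out of the trial for something that happened after randomisation. Intention to treat is meant to rule out exactly that.

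The primary outcome is measured in patients, so the practical question is what happens to a leaver's patients. If the cluster goes, its patients go too, although they were enrolled and may already have been trained. With 20 clusters, one or two such exclusions would be noticeable. The comparison would also no longer be wholly protected by randomisation, because who remains would depend partly on events after allocation.

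**Working it through.** **Order of events**

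1. GPs are invited and allocated in blocks of four (Recruitment and randomisation).
2. The GP inclusion visit follows allocation (same section).
3. GPs are seen again one year after that visit (GP Follow-up).
4. A departure in the year between steps 2 and 3 therefore falls after allocation, and the exclusion criterion as worded covers it.
5. The analysis is by intention to treat (Statistical analysis, General; Study limitations). Under that principle an allocated GP's patients stay in the allocated arm.

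Steps 4 and 5 cannot both be followed if exclusion of the GP extends to the patients. No section says that the criterion is judged only before allocation, or that a leaver's patients stay in the analysis.

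**Size of one cluster**

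Inputs: 267 patients and 20 GPs (Participants); 10 GPs per arm (Recruitment and randomisation). No figure of the plan is disputed here.

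- Patients per GP: 267 / 20 = 13.35, about 13.
- Share of the trial: 1 / 20 = 5%. Share of one arm: 1 / 10 = 10%.

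**Variance of the difference**

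Assume equal cluster sizes and the same between-cluster variance in both arms. The variance of the difference is then proportional to 1/k1 + 1/k2, where k1 and k2 are the numbers of clusters per arm.

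- As planned: 1/10 + 1/10 = 0.200.
- One lost: 1/9 + 1/10 = 0.211; ratio 0.211 / 0.200 = 1.056.
- Two lost from one arm: 1/8 + 1/10 = 0.225; ratio 0.225 / 0.200 = 1.125, that is, 12.5% more variance. The standard error rises by √1.125 = 1.061, about 6%.

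**Power, as an illustration only**

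The plan aims to "detect a 25 % difference between groups regarding the right performance of inhalation technique, with a power of 80 % and a confidence level of 95" %. It gives no control-group rate, so I assume 10%, 25% and 37.5%, each with a 25-point difference, a two-sided 5% test and the article's ICC of 0.1. The effective number per arm is k × m / (1 + (m − 1) × 0.1), entered in the normal approximation for two proportions. For patients per cluster, m, I take 13.35 (nobody lost) and 267 × 0.6 / 20 = 8.01 (the anticipated 40% loss).

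| Clusters | m = 8.01: control rate 10% / 25% / 37.5% | m = 13.35: control rate 10% / 25% / 37.5% |
|---|---|---|
| 10 v 10 | 0.84 / 0.71 / 0.69 | 0.92 / 0.81 / 0.79 |
| 9 v 10 | 0.82 / 0.69 / 0.66 | 0.90 / 0.79 / 0.77 |
| 8 v 10 | 0.79 / 0.66 / 0.63 | 0.88 / 0.76 / 0.74 |

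Each cluster lost from one arm costs about 2 to 3 points of power. The number of leavers is hypothetical, since the article gives no expected turnover.

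**The case against.** The strongest reply is that the criterion can be read harmlessly. It sits beside declining to take part, which is normally settled at invitation, and it may have been meant for GPs who already knew they would be leaving. GPs are invited before they are allocated, so such a screen is feasible and legitimate. This stands as a possible intention. The wording does not confine the rule to foreseen departures, however, and the inclusion visit comes after allocation.

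A second reply is that nothing says the patients leave with the GP. Their own exclusion criteria do not mention it, the research team measures their outcome, and the analysis is by intention to treat. On that reading only the GP-level follow-up is lost. This also stands. A reader might infer that whole clusters will certainly be removed; the article does not state that. The loss of patients is an implication of excluding the cluster, and the text neither confirms nor denies it.

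A third reply concerns bias. A reader might infer that departures would differ by arm. The article gives no evidence for this, and a training session of about 15 minutes is an unlikely reason to leave a post. Bias from post-randomisation exclusion is possible in principle, but neither its direction nor its size can be derived here.

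A reader might also take the remark in Study limitations that loss to follow-up "will be taken into account in performing data analysis (intention-to-treat analysis") as a commitment to analyse completers only. The article does not say so. The treatment of missing patient outcomes is commonly left to an analysis plan, which is not shown, and it is a separate matter from GP eligibility.

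**Conclusion.** The criterion as worded reaches past allocation and, read literally, conflicts with the intention-to-treat commitment. This is a rule the article states, so an analysis plan that is not shown does not remove the conflict in the protocol.

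The demonstrable size is modest: the cost in precision and power worked out above, and only if departures occur and clusters are in fact excluded. The variance figure rests on equal cluster sizes and equal between-cluster variance; the power figures rest also on assumed control rates. The more important reason to correct the wording is that it permits a post-randomisation exclusion whose effect on the estimate could not be checked afterwards.

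This should be fixed. Confidence is moderate, because a foreseen-departure reading is possible and the fate of a leaver's patients is left open.

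**What to change.** Two sentences are enough.

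1. In the GP exclusion criteria, limit the second item to departures already known before the GP is allocated.
2. In the statistical analysis section, state that once a GP is allocated, all of that GP's enrolled patients keep their 12-month assessment by the research team and are analysed in the allocated arm, whether or not the GP stays in post.

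The second sentence matters more for GPs already randomised. Trial status reports that recruitment has reached its second phase, so a reworded eligibility line cannot screen those allocated earlier.

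The cost is a wording change. No new procedure is needed, because the outcome visit already belongs to the research team. The small downside is that the estimated effect may be slightly diluted by patients whose GP left, for example before the 3- and 6-month reinforcement visits that the GP delivers. In a trial described as pragmatic, that dilution is part of how the intervention would work in routine care.
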